## Abstract

**Background:**

Despite continual improvements in the management of acute coronary syndromes, adherence to guideline-based medications remains suboptimal. We aim to improve adherence with guideline-based therapy following acute coronary syndrome using an existing service that is provided by specifically trained pharmacists, called a Home Medicines Review. We have made two minor adjustments to target the focus of the existing service including an acute coronary syndrome specific referral letter and a training package for the pharmacists providing the service.

**Methods/Design:**

We will be conducting a randomized controlled trial to compare the directed home medicines review service to usual care following acute coronary syndromes. All patients aged 18 to 80 years and with a working diagnosis of acute coronary syndrome, who are admitted to two public, acute care hospitals, will be screened for enrolment into the trial. Exclusion criteria will include: not being discharged home, documented cognitive decline, non-Medicare eligibility, and presence of a terminal malignancy. Randomization concealment and sequence generation will occur through a centrally-monitored computer program. Patients randomized to the control group will receive usual post-discharge care. Patients randomized to receive the intervention will be offered usual post-discharge care and a directed home medicines review at two months post-discharge. The study endpoints will be six and twelve months post-discharge. The primary outcome will be the proportion of patients who are adherent to a complete, guideline-based medication regimen. Secondary outcomes will include hospital readmission rates, length of hospital stays, changes in quality of life, smoking cessation rates, cardiac rehabilitation completion rates, and mortality.

**Discussion:**

As the trial is closely based on an existing service, any improvements observed should be highly translatable into regular practice. Possible limitations to the success of the trial intervention include general practitioner approval of the intervention, general practitioner acceptance of pharmacists' recommendations, and pharmacists' ability to make appropriate recommendations. A detailed monitoring process will detect any barriers to the success of the trial. Given that poor medication persistence following acute coronary syndrome is a worldwide problem, the findings of our study may have international implications for the care of this patient group.

**Trial registration:**

Australian New Zealand Clinical Trials Registry ACTRN12611000452998

## Background

Optimal medication management is critical to improving outcomes following acute coronary syndrome (ACS), yet prescribing practices and patient behaviors often fall below recognized targets [1-3]. Research demonstrates that the prescribing of guideline-based medications following ACS, including antithrombotics, beta-blockers, angiotensin-converting enzyme inhibitors, and statins, has improved over recent years [4] but is not yet ideal [3]. When patients with ACS leave hospital and return to the community, however, a more significant problem becomes apparent due to the premature discontinuation of guideline-based therapies by patients and/or clinicians [1-3]. Furthermore, the majority of the morbidity and mortality that occurs in the early post-discharge period can be attributed to a failure to appropriately use these existing medications [5-8]. For example, premature medication discontinuation, when measured at one month post-discharge in a myocardial infarction population, decreased 12-month survival by 8% [2]. While, understandably, much of the focus on improving patient outcomes following ACS has centered on the acute phase of care, it is crucial that more attention is paid to the development of new, post-discharge strategies to improve outcomes following hospital discharge.

Similar to other developed countries [2], poor medication persistence following ACS has been recognized as an unresolved problem in Australia [3,9]. A recent Australia-wide quality improvement study, called Discharge Management of Acute Coronary Syndrome (DMACS) utilized an education-based intervention to improve in-hospital, guideline-based prescribing and this resulted in a significant improvement in the proportion of patients prescribed four guideline-based medications at discharge, from 57% at baseline to 69% post-intervention (*P *< 0.0001) [3]. A telephone follow-up of the post-intervention group, however, revealed a 17% decline in the proportion of patients taking all four guideline-based medications at three months post-discharge. This equated to a 66% loss of the improvement in prescribing that was recorded at discharge, by just three months post-discharge and suggested that the intervention was effective at improving in-hospital prescribing, but there was little effect on long-term medication use. The authors noted in their discussion that further community follow-up once the patients were settled in their homes could improve the poor rates of post-discharge medication persistence.

### ACS post-discharge services

Cardiac rehabilitation has been continually shown to improve multiple outcomes following ACS, including mortality [10]. As such, the DMACS study also aimed to improve referral rates and uptake of cardiac rehabilitation. While post-intervention referral rates significantly increased from 67% to 73% (*P *= 0.001), attendance rates remained unchanged at just 33% [3], which is in line with the low worldwide attendance rates for cardiac rehabilitation programs [11]. A Cochrane review has highlighted the potential for structured interventions to successfully increase cardiac rehabilitation uptake; however, interventions aimed at improving cardiac rehabilitation completion rates have generally proven less successful [12]. Although the benefits of cardiac rehabilitation are well-established, attendance and completion rates remain low, and evidence-based strategies to overcome these problems and increase access to the service are yet to be recognized.

Cardiac rehabilitation programs are designed to increase adherence to both pharmacological and non-pharmacological therapies [13]. However, there have been few evaluations of the specific effect of these programs on medication adherence. One study of a relatively high-intensity cardiac rehabilitation program was able to demonstrate an improvement in medication adherence at three months post-discharge [14], but despite these initial improvements, the benefit was short-lived, with both treatment and control groups reporting the same level of medication adherence at six months post-discharge. There is a clear need for a more intensive multidisciplinary approach to the post-discharge management of ACS, including interventions specifically directed at improving medication management. These interventions should be designed to both complement and promote the existing cardiac rehabilitation programs, as well as being accessible to the large majority of patients who currently find reasons not to attend cardiac rehabilitation.

The Home Medicines Review (HMR) program is an existing community-based service that has the potential to be tailored to meet the needs of patients recently discharged from hospital following ACS. Although this potential has not been fully realized in the past [15], HMRs may be used to particularly target patients' persistence and adherence to guideline-based medications following ACS. The HMR service currently involves general practitioner (GP) referral of patients to an HMR-accredited pharmacist, often through a community pharmacist liaison [16]. The accredited pharmacist will visit the patient in their home, discuss their medication taking habits, and provide education or adherence interventions where required. Following the home visit the accredited pharmacist writes a report for the GP noting their observations and any clinical adjustments that could be made to the patient's medication regimen. Based on this report, the GP is expected to complete an agreed management plan, selecting the accredited pharmacist's recommendations which they agree to implement and/or follow up. The service is currently available in Australia, free of charge to Australian citizens under funding arrangements through the public health system, Medicare Australia. The GP, accredited pharmacist, and community pharmacist involved with an HMR service are paid by way of reimbursement from Medicare Australia. One of the eligibility criteria for HMRs is recent hospital discharge [16] and the HMR service has been demonstrated to be feasible as a post-discharge service for patients following ACS in the Australian healthcare setting [17]. However, the effect of this service on clinical outcomes following ACS is unknown.

### Justification for this trial

Programs allowing pharmacists to provide formal medication review services exist across many countries. Although there are some regional differences in the structure of these programs, they are generally designed to improve the quality use of medicines and minimize the potential for medication-related harm. Previous studies assessing patient outcomes following post-discharge medication review services have found conflicting results. The HOMER trial questioned the value of the service as the intervention group had an increased hospitalization rate at six months post-discharge [18]. Similarly, Barker *et al. *trialed a home-based, post-discharge medication review service in patients with congestive heart failure (CHF) and found that patients in the intervention group had significantly longer CHF hospital stays, incidence rate ratio = 2.34 (*P *< 0.001) [19]. There were no statistical differences in the other two primary outcomes of death and hospital readmission rates. Conversely, Stewart *et al. *were able to demonstrate both a short- and long-term benefit by reducing hospital readmissions and mortality, following a post-discharge service targeted at a population that was suspected to be at a high risk for readmission [20,21]. While the goal of reducing healthcare costs through fewer and shorter hospitalizations appears appropriate, this outcome may not be a suitable measure for a service focusing specifically on medication management. A review by Benbassat *et al. *questioned the validity of hospital readmissions as a marker for quality care and highlighted that the length of hospital stays, readmission rates, and death appear to be mostly predicted by unmodifiable causes, such as age, disease severity, and co-morbidity [22]. The authors concluded by highlighting the importance of improving other 7clinical outcome measures, such as adherence to guideline-based therapy and improving patient's self-management abilities.

Although the interventions trialed in their studies included a significant focus on improving medication adherence, neither Holland *et al. *nor Barker *et al. *measured changes in this outcome. As such, both authors were left to speculate over this outcome and how it may have affected hospital readmission rates. Conversely, Stafford *et al. *conducted a prospective, non-randomized, controlled cohort study of a pharmacist-led service aimed at improving warfarin therapy post-discharge and, while there were no significant changes in readmission or death rates over the 90-day follow-up period, the intervention was associated with a reduced rate of adverse bleeding events from warfarin therapy, 5.3% *vs*. 14.7% (*P *= 0.03) and increased persistence with therapy, 95.4% *vs*. 83.6% (*P *= 0.004) [23]. The pharmacists involved in this trial were HMR-accredited, but also received additional education, specific to the needs of patients taking warfarin [24]. This ability to focus the HMR service on specific patient groups has been proposed as an avenue for improvement of the HMR service and this warrants further attention through future research [15]. We have considered both of these aspects in the modification of the service planned for this trial and have outlined that the period following hospital discharge is an appropriate time to target ACS patients due to their risk for harm resulting from premature medication discontinuation [2,3]. Furthermore, we have developed a detailed education program to help pharmacists address ACS-specific issues and encourage patient behavior change by using a motivational approach to the HMR patient interview.

### Objectives

In this study, we aim to investigate the effect of an adaptation of the currently available HMR service on guideline-based medication adherence and persistence following ACS. The service will be directed towards the needs of ACS patients by educating the accredited pharmacists involved about ACS-specific patient issues and through improving the continuum of care by providing consistent information in a structured HMR referral letter. As such, the trialed service will be termed a directed Home Medicines Review (dHMR). This is the first trial in a series of studies entitled 'Medication Reviews ReDirected (MedReDi)' which refers to the plan for future research in this area, following a similar theme of minor adjustments to the currently existing HMR service, so that patients with other specific illnesses can be targeted through new dHMR services. The overall intention will be to help patients become more familiar and competent with their medication management aspect of therapy - more simply, helping patients become 'MedReDi'.

For the purpose of this study, guideline-based ACS medication therapy refers to the four medication classes as supported by ACS guidelines [25-27]. These medication classes include: angiotensin-converting enzyme (ACE) inhibitors/angiotensin II receptor blockers (ARBs); antithrombotics (aspirin and/or clopidogrel/prasugrel and/or warfarin); beta-blockers; and statins.

## Methods/Design

### Overview

We will conduct a randomized controlled trial comparing the dHMR service delivered at two months post-discharge to usual care following an ACS admission. Changes in the pharmacist referral process and an ACS-specific education package to be completed by the study pharmacists make this program different to the standard HMR service. The primary outcome will be the proportion of patients who are adherent to a complete, guideline-based ACS medication regimen at six and twelve months post-discharge. Patients will be enrolled in hospital during an admission for ACS. Figure 1 provides an overview of the trial protocol. The design of the intervention and monitoring system has been based on a conceptual framework for the standardized evaluation of chronic disease management interventions, as developed by Lemmens *et al. *[28]. Figure 2 is a summary of this framework and Figure 3 is a comparison of how the components of this trial compare against the Lemmens *et al. *framework.

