### Outcomes

All outcomes will be measured using blinded assessment processes at the two study endpoints of six and twelve months post-discharge. Each outcome will be a comparison between the control and intervention groups. A proposed conceptual framework for the standardized evaluation of chronic disease management interventions has been considered in the selection of the trial outcomes and further trial evaluation [28]. Using a framework to guide outcome selection has not only helped to ensure that we are measuring the important clinical outcomes from the intervention, but also highlighted the individual steps of the intervention that require monitoring. Monitoring these individual steps, such as pharmacist detection of drug-related problems and GP acceptance of pharmacist recommendations, is important to measure the level of alignment between the theoretical plan and the practical application of the intervention. Such detailed monitoring and outcome reporting may also elucidate areas of practice worthy of further focus in future research.

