### Primary outcome

The primary outcome will be the proportion of patients who are adherent to a complete, guideline-based ACS medication regimen at the trial endpoints. The accepted definition of adherence for this trial will be a medication possession ratio (MPR) of 80% to 120% for all guideline-based medications, which is a commonly accepted cut-off for this measure [35-39]. MPR will be determined by dividing the total number of days of medication supplied by the total specified time period. This value can be multiplied by 100 in order to be reported as a percentage of the time that the patient had medication available to take, a commonly used surrogate measure of adherence. During the baseline interview, we intend to record all possible pharmacies that a patient may attend in order to make the dispensing records complete. If, however, there is a significant shortfall in the completeness of dispensing records, we will use self-report of medication adherence as an alternate measure. The four-item Morisky adherence questionnaire will be used for this purpose [40]. This is a well-validated instrument, being used previously with good predictive validity in patients at risk of cardiovascular disease [40,41]. In the case where a patient has a clearly documented contraindication to one of the four guideline-based medication classes, their medication regimen may still be considered 'complete' provided they are taking all other guideline-based medications. For example, a patient with asthma not taking a beta-blocker but still taking aspirin, an ACE inhibitor, and a statin, will be considered in the same group as those prescribed all four medications. This primary outcome comprehensively assesses the overall impact of the intervention on both GP prescribing behaviors and patient medication-taking behaviors. In order to separately measure the recognized problem of persistence with guideline-based medications, we will complete a secondary analysis of the primary outcome in the group of patients who are prescribed a complete, guideline-based medication regimen at the time of discharge from hospital.

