### Sample size

We are aiming to detect a change in the primary outcome of 15% between the control and intervention groups. This predicted change is based on the results of the DMACS study, whereby a 12% post-intervention improvement was observed on the proportion of patients taking the same four guideline-based medications at discharge [3]. To detect a change of 15%, assuming a control group result of 45%, a power to detect a difference of 80% with alpha = 0.05, we require a minimum sample size of 186 patients per group. To account for an approximate dropout rate of 20%, we aim to enroll 465 patients in total.

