### Statistical analysis

All baseline variables will be compared between the control and intervention groups using independent samples t-tests for continuous variables and chi-squared analysis for categorical variables. All outcomes will be reported as descriptive comparisons between the control and intervention groups, with significance reported at alpha = 0.05. Where primary outcomes reach statistical significance, any noted difference in the baseline group comparison will be tested by univariate comparison with stepwise addition into a multivariate model for those with univariate significance of *P *< 0.1. Changes in each group's questionnaire results between baseline and study endpoints, as well as differences between intervention and control group's questionnaire results, will be reported. Further correlational investigations between questionnaire results and adherence will be reported elsewhere. As there are several potential barriers that may prevent a patient randomized to the intervention group from receiving a dHMR according to the protocol, we will use both an intention-to-treat analysis as well as an on-treatment sensitivity analysis.

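### Adherence at six and at twelve months are both primary, unranked and each judged at 0.05, while the sample size covers one test at an unnamed time point

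*Protocol article*

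**What the plan says.** All references are to the protocol article.

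- **Abstract, Methods/Design:** "The study endpoints will be six and twelve months post-discharge".
- **Overview:** the primary outcome is the proportion of patients "adherent to a complete, guideline-based ACS medication regimen at six and twelve months post-discharge".
- **Outcomes:** all outcomes are "measured using blinded assessment processes at the two study endpoints of six and twelve months post-discharge".
- **Primary outcome:** the definition is repeated as "adherent to a complete, guideline-based ACS medication regimen at the trial endpoints", again for more than one endpoint.
- **Statistical analysis:** "All outcomes will be reported as descriptive comparisons between the control and intervention groups, with significance reported at alpha = 0.05". The next sentence starts "Where primary outcomes reach statistical significance", in the plural, and makes that significance the trigger for covariate modelling.
- **Sample size:** "We are aiming to detect a change in the primary outcome of 15% between the control and intervention groups". With a control proportion of 45% and "a power to detect a difference of 80% with alpha = 0.05, we require a minimum sample size of 186 patients per group", the target is 465 after allowing for 20% dropout. No time point is attached to any of these figures.

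No section ranks the two time points, divides alpha between them, requires both to succeed, or describes one analysis that combines them.

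**The concern.** Each time point yields its own proportion and its own comparison of groups. Followed as written, the plan produces two primary tests at 0.05 and no statement of what makes the trial positive.

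This matters most if the two results disagree, which is a realistic prospect here. The intervention is a single home review at about two months (Intervention). The Background section on post-discharge services describes a rehabilitation programme whose adherence gain at three months was gone by six. A benefit at six months that has faded by twelve would leave readers free to call the trial positive or negative.

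The sample size inherits the gap. It is sized for one test, so the stated 80% power describes the trial's chance of success only if one time point decides.

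**Working it through.** **Inputs.** From Sample size: control 45%, difference 15 points (so 60% in the intervention group), 80% power, alpha 0.05, 186 per group, 20% dropout, 465 in total. A two-sided test is not stated but is inferred, because only a two-sided test reproduces 186. The correlation between the six- and twelve-month test statistics is not given, so it is varied as an assumption.

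**1. The plan's own figure.** With mean proportion 0.525:
- A = √(2 × 0.525 × 0.475) = 0.7062
- B = √(0.45 × 0.55 + 0.60 × 0.40) = 0.6982
- n = [(1.960 × A + 0.842 × B) / 0.15]² = 172.8, so 173 without continuity correction
- With the correction: (172.8/4) × [1 + √(1 + 4/(172.8 × 0.15))]² = 185.9, so **186**
- Total: 2 × 186 / (1 − 0.20) = **465**

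One-sided versions give 136 (uncorrected) and 150 (corrected). The stated figures are right for one two-sided test. Power at 186 per group is 80.0% with the correction and 82.8% without.

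**2. If either time point counts as success.** Under no effect, the chance of at least one significant result is 1 − P(|Z₁| < 1.96 and |Z₂| < 1.96), with Z₁ and Z₂ bivariate normal with correlation ρ. For ρ = 0 this is 1 − 0.95² = 0.0975. A false claim of benefit is 1 − P(Z₁ < 1.96 and Z₂ < 1.96).

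| Assumed ρ | Any false positive (two-sided) | False claim of benefit |
|---|---|---|
| 0 | 9.75% | 4.9% |
| 0.5 | 9.1% | 4.5% |
| 0.8 | 7.8% | 3.9% |
| 0.9 | 7.0% | 3.5% |
| 0.98 | 5.9% | 3.0% |
| one test only | 5.0% | 2.5% |

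The high-correlation rows matter. Primary outcome defines the possession ratio as days supplied over the specified period. If the twelve-month period includes the first six months, the two measures share data and ρ could exceed 0.9.

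**3. If both time points must be significant.** The error rate cannot exceed 5%. Power is P(both significant), assuming the same 15-point effect at each. Without continuity correction, each test succeeds when a standard normal variable lies below (0.15 − 1.960 × A/√186) / (B/√186) = (0.15 − 1.960 × 0.05178) / 0.05120 = 0.9475.
- ρ = 0: 0.8283² = 68.6%
- ρ = 0.5: 72.7%
- ρ = 0.8: 76.4%
- ρ = 0.9: 78.3%

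At ρ = 0.98 the same calculation gives 80.8%, so without the correction the shortfall disappears at very high correlation. With the continuity correction that reproduces 186, the limit is (0.15 − 1/186 − 1.960 × 0.05178) / 0.05120 = 0.8425. Joint power is then 64.0% at ρ = 0, 75.0% at 0.9 and 77.8% at 0.98, below 80% throughout.

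**4. If one time point is primary.** Step 1 applies as it stands: 186 per group, 465 in total, 5% error and 80% power.

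**The case against.** The strongest reply is that the article states no either-one-wins rule. Wording that names six and twelve months can mean that both are required, or simply that results are reported at each. Statistical analysis calls the comparisons descriptive and gives 0.05 as a threshold for each; it promises no family-wise rate. Handling of multiplicity is often left to an analysis plan, which is not shown here.

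Much of this stands. A reader might infer that the trial's false-positive rate simply is 7-10%. The documents do not support that: the range depends on a decision rule the article does not give and on a correlation it does not report, and overlapping measurement periods could bring the rate to about 6%. A reader might also infer that the sample size contradicts the decision rule. It does not, because there is no rule to contradict and 186 and 465 both reproduce exactly. Nor does the article break a promised 5% trial-wide error rate, since it promises none.

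What does not stand is the suggestion that nothing needs correcting. The article itself declares two primary time points in several sections. It attaches significance to them, lets that significance trigger further modelling, and powers a formal test. An analysis plan that named one time point would disagree with this text, so the text needs changing in either case.

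**Conclusion.** The point holds in a limited form. Two primary time points are declared, each at 0.05, without ranking or a rule for combining them, and the correctly calculated sample size covers one test at an unnamed time point.

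The size depends on how the gap is filled:
- Either suffices: two-sided error of about 6-10%, and a false claim of benefit of about 3-5% instead of 2.5%, for assumed correlations from 0.98 down to 0.
- Both required: error at or below 5%, but joint power of about 69-78% (uncorrected, correlation 0 to 0.9, equal effects at both times).
- One primary: the stated error and power both hold.

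Only the third reading delivers the stated 5% and 80% whatever the correlation, and the article does not select it.

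**What to change.** Before recruitment, which Trial status says has not begun:

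1. Name one time point as primary. Make the other a key secondary outcome, tested at 0.05 only if the first is significant.
2. In Sample size, state that the 45% control proportion, 20% dropout and 80% power refer to the named time point, and confirm that the first two are plausible there. Nothing in the article ties them to either six or twelve months.
3. Align the Abstract, Overview, Outcomes, Primary outcome and Statistical analysis, and use the singular for the primary outcome.

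The cost is a short text change in six places. Provided the assumptions in item 2 are confirmed, 186 per group and 465 in total stay as they are. The downside is that a significant result at the other time point alone could not be claimed as trial success.
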